## 5 SCIENTIFIC CONTEXT OF THE STUDY

About 40% of patients treated for breast cancer frequently complain of sleep disorders. Insomnia is the most frequent one. The prevalence of insomnia complaints is higher in breast cancer patients than in other types of cancer, and is also higher than in the general population (between 20% and 70% in breast cancer patients vs. 30% in the general population) . A recent study indicates that sleep complaints concern 25% of patients even before diagnosis, and 46% (including 18% complaining of insomnia) at the time of diagnosis, showing the negative impact of the announcement of the pathology on subjective sleep quality, and in particular on symptoms suggestive of insomnia . However, objective evidence of sleep patterns's modifications in breast cancer remains scarce and inconclusive (see  for review). In particular, previous studies have focused only on the effects of chemotherapy and have not always included a control group, limiting the scope of their results. The links with cognitive and psychopathological processes, as well as the underlying mechanisms, are not clearly demonstrated in this pathology. Finally, taking into account patients' complaints, it seems necessary to limit sleep disorders in breast cancer in order to improve patients' quality of life using non-medicinal, easy-to-implement approaches.

### 5.1 CURRENT STATE OF KNOWLEDGE

Sleep difficulties in breast cancer remain poorly studied in a precise and integrated way (i.e. taking into account all the processes involved in sleep regulation). Indeed, sleep is intrinsically linked to circadian rhythms, with circadian rhythmicity in humans reflected by a spontaneous alternation of periods of sleep and activity over 24 hours, i.e. the activity-rest rhythm. Previous studies have shown deregulation of the activity-rest rhythm in breast cancer before and during chemotherapy  but also in patients not treated with chemotherapy . Of these studies, only three, including one from our work, included a control group with no history of cancer . The results have shown a longer total sleep time and a longer duration of naps during chemotherapy compared with the period before initiation of treatment  and in comparison with controls free of cancer. In addition, the activity-rest rhythm appeared to be less ample in breast cancer patients who had not received chemotherapy, compared with subjects with no history of cancer . Conversely, Li and colleagues showed that initiation of chemotherapy, compared with pre-treatment assessments and the end of chemotherapy, was associated with shorter total sleep time, as well as more frequent awakenings and poorer sleep quality . Beck and colleagues also report a shorter total sleep time on the first night after chemotherapy initiation, compared with before and after the treatment period . Finally, Kuo and colleagues found no difference between assessments before and during chemotherapy . The results concerning the effects of chemotherapy on sleep parameters measured by actigraphy are therefore highly variable, and do not allow to draw definitive conclusions as to sleep alterations as measured by actigraphy . A literature review published in 2015  reported, however, that chemotherapy could accentuate sleep difficulties already present before the initiation of treatment in breast cancer.

In contrast to actigraphic studies, polysomnographic (PSG) studies, the *gold-standard* of sleep assessment, are still scarce. As a result, alterations in the structure of sleep in this pathology are not clearly described. In addition, PSG makes it possible to quantify parameters associated with sleep structure and memory consolidation. Its use therefore provides a better understanding of sleep changes than actigraphy, which remains an indirect approach to quantif

sleep quality and quantity. Previous PSG studies suggested alterations in sleep quality and quantity following chemotherapy treatment. Parker and colleagues compared the sleep architecture of patients treated for advanced non-cerebral cancer (stage 3 or 4 cancers), including 32 patients treated for breast cancer (28% of the cohort) . The results have shown reduced sleep efficiency and sleep stage durations in these patients, compared with the norms established by Williams and colleagues in healthy participants . Roscoe and colleagues  revealed that after the end of chemotherapy, patients slept more than before the start of chemotherapy. This result could be explained by poor sleep quality at baseline due to the stress associated with cancer diagnosis and the apprehension of chemotherapy, or by an accumulation of fatigue and sleep deprivation during treatment, leading to compensation at the end of treatment.

These studies have shown changes in the sleep's macrostructure in patients treated for breast cancer, but they have several limitations that prevent a precise understanding of the impact of cancer and treatment on sleep. The absence of a control group in several of these studies is the main limitation. Indeed, the presence of a control group with no history of cancer and a group without treatment makes it possible to determine whether changes in sleep architecture are secondary to the cancer itself or to treatment. In addition, the inclusion of heterogeneous populations in terms of age and cancer type may have limited the statistical power of the studies' results, and prevented changes in sleep architecture from being revealed. In addition, no studies have assessed changes in sleep patterns prior to initiation of chemotherapy. PSG also provides detailed information on the macro- and micro-structure of sleep, enabling links to be made with cognitive performance and the detection of potential sleep disorders such as apnea. New studies, more homogeneous in terms of eligibility criteria, but also longitudinal, are needed to determine the presence of sleep disorders in breast cancer patients. A better understanding of these sleep disturbances will also enable to determine their possible contribution to the onset of cognitive and psychopathological deficits.

Patients with breast cancer suffer not only from impaired episodic memory, but also from impaired executive functions. The latter are particularly involved in a particular form of episodic memory, spatial memory, which has so far received little attention in breast cancer. This type of memory enables to remember a route or find objects in different places, and is therefore essential for everyday life. What's more, it relies on the integrity of the hippocampus, a region that appears to be affected in women with breast cancer . Sleep disturbances are also known to impair executive functions involving the prefrontal cortex  and the cognitive control mechanisms that depend on it. These cognitive control mechanisms enable the regulation of behavior in complex situations, particularly after a stressful event. In breast cancer, sleep disorders could have a negative impact on these control mechanisms, leading to reduced resistance to stress.

In addition to the beneficial effects of sleep on cognitive processes, particularly memory and executive functions , sleep plays an important role in the stress response in healthy subjects and in various pathologies . Cancer diagnosis, as well as the situation associated with the pathology, constitute a major source of stress. However, as is the case in the general population, patients do not react homogeneously to these situations. Sleep disorders could influence the way patients react to stressful situations, such as those associated with their care pathway. There is a need to understand to what extent sleep influences psychopathological processes in breast cancer, so that it is possible to improve supportive care throughout cancer trajectory.

## 5.2 ALREADY EXISTING CARE METHODS AND THEIR LIMITATIONS

Sleep and circadian rhythm disturbances are common in breast cancer, and need to be managed. Cognitive-behavioural therapies and physical activity are currently proposed as non-medicinal approaches. However, although positive effects have been reported on mood, quality of life and sleep complaints, their beneficial effects on the quality and quantity of sleep measured by PSG in breast cancer are not clearly established . Moreover, these approaches do not specifically target sleep and/or circadian rhythm disturbances. Promising results suggest that the vestibular system may be involved in circadian regulation and resynchronization . Similarly, recent studies have shown the positive effects of vestibular system stimulation *via* sleep balancing on sleep quality in healthy subjects. Finally, recent results from the COMETE team (doctoral thesis by [name], Dir: [name]) suggest that stimulation of the vestibular system, particularly galvanic stimulation, could have an effect on the circadian rhythms . The use of vestibular system stimulation therefore appears particularly appropriate for specifically improving sleep and resynchronizing rhythms in breast cancer. This could be achieved using galvanic vestibular stimulation (GVS), based on stimulation of the peripheral vestibular organ through activation of vestibular afferents, by applying an electric current between the two mastoids. GVS has been used for many years to safely and painlessly stimulate the vestibular system  but more recent studies have also demonstrated the feasibility and positive effects of GVS on cognition  and anxiety levels  in healthy participants. GVS has no particular contraindications and could therefore be offered to all participants.

## 5.3 DESCRIPTION OF THE PROPOSED NEW TREATMENT

The GVS will be performed using a device available from U1075 (Caen, Dir: [name]), a team specializing in remediation related to biological rhythms, notably through vestibular stimulation. The device used is distributed by Soterix médical and is CE marked (<https://soterixmedical.com/research/vestibular>). This equipment enables vestibular afferents to be stimulated autonomously and in a pre-regulated way: the stimulation level is pre-programmed and cannot be modified without being the administrator of the device, ensuring precise and safe stimulation. In order to determine the most accurate and effective stimulation protocol possible, the device is currently being evaluated in our laboratory on cancer-free participants as part of a Master's 2 internship, and no side effects have been reported. In addition, the COMETE unit (Dir: [name], work by [name]) is currently carrying out a protocol (VELOCCE project NCT05030389) on elderly people with no pathologies. Similarly, no side effects were reported by participants. All these results demonstrate the safety, feasibility and ease of use of the Soterix GVS device to be used in the ICANSLEEP protocol. The stimulation protocol (effective stimulation, GVS, or non-effective stimulation, SHAM) will be carried out remotely, five times a week in the morning for two weeks, using a securely accessible videoconferencing platform available on the Université de Caen network. Participants will be able to connect *via* a computer at the times and on the days indicated by the experimenters. Once connected, they will be able to videoconference with a professional from the research team, who will check the correct position of the electrodes and note the participants' behavior. These videoconferences will also help to ensure that the conditions are consistent between sessions and between participants.

[name]'s recently defended thesis (supervised by [name]) demonstrated the tolerance and beneficial effects of galvanic stimulation on anxiety and circadian rhythms.

Publications using Soterix brand GVS equipment have recently been published, attesting to its safety and feasibility of use .

#### 5.4 MAIN OBJECTIVE

The project has two main aims, each with its own main objective.

**Axis 1:** To characterize the sleep of patients undergoing breast cancer treatment before and after adjuvant chemotherapy, compared with patients not treated with chemotherapy and with women free from history of cancer.

**Axis 2:** To explore the regulatory effect of galvanic vestibular stimulation (GVS) on circadian rhythms in patients undergoing treatment for localized breast cancer, compared with SHAM stimulation (not effective).

#### 5.5 SECONDARY OBJECTIVES

##### Axis 1:

- 1)
  - a) To assess the effects of cancer and chemotherapy on sleep and circadian rhythms
  - b) To determine whether the presence of sleep disorders is associated with altered circadian rhythms
- 2) To assess the effects of cancer and chemotherapy on cognitive abilities and their neuro-functional correlates
- 3) To assess the effects of cancer and chemotherapy on cortical structure
- 4) To assess the effects of cancer and chemotherapy on functional connectivity at rest
- 5) To evaluate the link between sleep disorders and:
  - a) Cognitive abilities and their neuroanatomical correlates
  - b) The stress-related physiological systems
  - c) Quality of life

##### Axis 2:

- 1) To evaluate the effects of GVS on:
  - a) Circadian rhythms
  - b) Spatial memory
  - c) The stress-related physiological systems
- 2) To assess the effects of rhythm resynchronization on sleep quality
- 3) To determine whether improved sleep is accompanied by better cognitive performance and quality of life

## 6 RESEARCH HYPOTHESIS AND EXPECTED RESULTS

##### Axis 1:

- 1)
  - a) Sleep and circadian rhythms would be altered in patients before chemotherapy compared with cancer-free subjects. Chemotherapy would exacerbate these effects compared with the no-chemotherapy group
    - For sleep, more awakenings lasting more than a minute and poorer sleep quality are expected.

- For circadian rhythms, the sleep/wake and cortisol rhythms are expected to be less ample.
- b) Altered rhythms have deleterious effects on sleep quality**
- 2)** Cognitive abilities would be more impaired after than before chemotherapy, whereas no decline is expected in patients not treated with chemotherapy and in healthy subjects. More specifically, this decline is expected to affect:
    - Spatial and episodic memory
    - Working memory
    - Executive and attentional functions
    - Functional connectivity during the ANT (Attentional Network Test) task, particularly within the orientation and cognitive control networks
  - 3)** After chemotherapy, the cortical structure should be altered, particularly in the regions involved in the above-mentioned cognitive abilities (i.e., hippocampus, frontal regions, cerebellum) compared to before chemotherapy, and compared to patients not treated with chemotherapy and healthy subjects.
  - 4)** For both groups of patients, the dynamics of functional connectivity at rest prior to chemotherapy should be altered, with greater ruminations than in the healthy group.
  - 5) a)** Sleep disturbances (independently of the effects of anxiety and depression) are thought to be linked to cognitive abilities and their neuro-anatomical correlates, specifically:
    - Episodic and spatial memory performance
    - White matter structure and functional connectivity
  - b)** Sleep disturbances are also associated with hyperactivity of physiological stress systems
  - c)** Sleep disturbances are associated with a lower quality of life

## **Axis 2:**

- 1)** GVS would allow :
  - a)** Resynchronizing circadian rhythms (i.e. acrophase) and amplifying the sleep/wake rhythm as the procedure progresses and the cortisol rhythm at the end of the procedure.
  - b)** Improving spatial memory performance compared to T2
  - c)** Reducing hyperactivity of stress-related physiological systems
- 2)** Resynchronizing rhythms improves sleep quality
- 3)** This improvement in sleep quality is associated with better cognitive recovery and quality of life following the course of treatment, compared with the absence of GVS.

## **7 JUDGING CRITERIA**

### **7.1 MAIN CRITERION**

**Axis 1:** The primary endpoint is sleep efficiency (ratio of total sleep time to time spent in bed) and the number of awakenings lasting more than one minute. These data are derived from polysomnography.

**Axis 2:** The main criterion selected are amplitude (corresponding to half the maximum variation in the rhythm under consideration) and acrophase (i.e. the time of day when activity or cortisol is highest). Changes in sleep/wake rhythms will be quantified over the 2-week

intervention period, and will be derived from actigraphy. Changes in cortisol rhythm will be measured using saliva samples obtained at T2 and T3.

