#### 8.3.1 Patient inclusion criteria

- Patient aged 45 to 65
- Patient with localized breast cancer, whether or not to start adjuvant chemotherapy
- Patient with education level 3 "end of primary education" (Barbizet scale)
- Patient fluent in French
- Patient having signed consent to participate in the study
- Patient with sleep complaints (ISI > 7)
- Patient with access to the Internet from a home computer

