**Axis 2:** In order to assess the effect of galvanic vestibular stimulation on circadian rhythms, the evolution of circadian rhythm parameters measured by actigraphy during the 2-week intervention (in particular the amplitude and phase of the activity-rest rhythm) will be described by a linear mixed model. The model will include a time effect, an intervention effect (GVS or SHAM) and a time x intervention interaction (parameter of interest to assess whether GVS has an effect on the evolution of circadian rhythm compared with SHAM), and will be adjusted for group (patients or controls) and possibly treatment (chemotherapy or not). To meet secondary objectives, sleep parameters, cortisol levels, cognitive abilities and quality of life assessments will be described before (T2) and after intervention (T3) in each group of patients (GVS or SHAM) and controls (GVS only) and compared pre-post GVS by a McNemar test or a Student (or Wilcoxon) test for paired series. Alternatively, the effect of GVS on sleep, cognitive ability

and quality of life at T3 could be tested in linear or logistic models adjusted for parameters at T2.

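### The Axis 2 acrophase criterion is a signed clock time with no stated direction, so it cannot by itself separate resynchronisation from no effect or from a plain shift

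*Protocol*

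**What the plan says.** The main objective of Axis 2 (protocol section 5.4) is "To explore the regulatory effect of galvanic vestibular stimulation (GVS) on circadian rhythms in patients undergoing treatment for localized breast cancer", compared with SHAM.

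The hypothesis (section 6, Axis 2, item 1a) is "Resynchronizing circadian rhythms (i.e. acrophase) and amplifying the sleep/wake rhythm as the procedure progresses". It has two parts. The amplitude part has a direction, since the rhythm should become larger. The acrophase part has none: no advance, delay or target time is given.

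Section 7.1 sets the criterion in two halves. The first reads "The main criterion selected are amplitude (corresponding to half the maximum variation in the rhythm under consideration"; the second is "acrophase (i.e. the time of day when activity or cortisol is highest".

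In section 12.2 the evolution over the two weeks of stimulation, "in particular the amplitude and phase of the activity-rest rhythm) will be described by a linear mixed model", has a time effect, an intervention effect and their interaction. The interaction is the "parameter of interest to assess whether GVS has an effect on the evolution of circadian rhythm compared with SHAM". Adjustment is for group and possibly for chemotherapy.

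On sleep, patients enter with "Patient with sleep complaints (ISI > 7" (section 8.3.1). No criterion concerns the timing of the rhythm. Section 9.1.1 measures circadian typology with the Horne and Ostberg questionnaire, from strongly morning to strongly evening, but typology is neither an eligibility criterion nor a term in the model.

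**The concern.** To resynchronise is to bring a misplaced phase back towards where it should be. For a late woman this means an earlier acrophase, and for an early woman a later one. Both are successes under the hypothesis, but they carry opposite signs on the clock. The interaction in section 12.2 compares mean signed courses, so it adds the two and they offset each other.

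The converse also holds. If GVS moved every woman by the same amount in one direction, the interaction would be non-zero whether the move was towards or away from the appropriate phase.

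What is at stake is how the acrophase half of the criterion can be read. Hypotheses 2 and 3 of Axis 2 build on it, because they link resynchronisation to better sleep, and better sleep to cognition and quality of life.

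**Working it through.** **Inputs from the protocol.** There are 50 patients (section 12.1), randomised to GVS or SHAM (section 8.1). No allocation ratio, alpha, SD or effect size is given, and section 12.1 says that there is no power calculation. There is therefore no figure of the plan's own to reproduce.

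**Assumed.** 25 versus 25 patients, two-sided 5%. Each GVS patient loses a fraction c of her deviation d from a reference phase; SHAM patients lose nothing.

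**Step 1, expected signed difference.** The change is −c·d in each GVS patient and 0 in each SHAM patient, so the expected GVS-SHAM difference is −c × mean(d). If deviations have typical size D and a share p of women are late, mean(d) = D(2p − 1). With c = 0.5 and D = 1.5 h:

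- p = 0.5: −0.5 × 1.5 × 0 = 0 h
- p = 0.7: −0.5 × 1.5 × 0.4 = −0.30 h
- p = 1.0: −0.5 × 1.5 × 1 = −0.75 h

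**Step 2, power under that mix** (SD of d 0.5 h; t-test on pre-post change with noise SD 0.75 h; 4,000 runs):

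| Share late | Signed acrophase | Absolute distance from reference |
|---|---|---|
| 50% | 5% | 89% |
| 60% | 9% | 90% |
| 70% | 21% | 89% |
| 80% | 44% | 89% |
| 90% | 70% | 89% |
| 100% | 93% | 89% |

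Slopes over 14 days, closer to the section 12.2 model (daily noise SD 1.0 h, 2,000 runs), show the same pattern. The signed measure has 6% at a 50:50 mix, 35% at 80:20 and 84% when all are late; the absolute distance has 72% to 74% throughout.

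**Step 3, a continuous spread** (d normal, measurement SD 20 min, 20,000 runs). With the sample centred on the reference and c = 0.5, SDs of 45, 60 and 90 min give 5% each for the signed measure and 53%, 77% and 96% for the absolute distance. With c = 0.3 they give 5% each against 26%, 41% and 72%. At SD 60 min and c = 0.5, a baseline phase × intervention term reaches 95%. If the sample is late on average, the signed measure recovers: 31% at a mean offset of 30 min and 84% at 60 min, against 84% and 97% for the absolute distance.

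**Step 4, where the alternative does worse.**

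- A uniform 30 min shift in a centred sample (SD 60 min) is found by the signed acrophase in 96% of runs and by the absolute distance in 10%.
- Steps 2 and 3 give every woman the same correct phase. Keep the total SD at 60 min and c at 0.5, but split the variance equally between harmless typology differences and true misplacement. The absolute-distance power falls from about 76% to about 21%. With typology SD 52 min and deviation SD 30 min it is about 10%. A baseline-phase interaction that ignores typology loses power for the same reason.

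**The case against.** A reader might infer that the acrophase criterion cannot test the hypothesis at all, that a null result would carry no information, or that a working intervention would go unseen by Axis 2. The documents do not support any of these.

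- Amplitude is the other half of the main criterion and has a stated direction. Cancellation of phase shifts does not touch it.
- Cancellation needs early and late women in the same sample. The protocol gives no distribution of acrophase; its eligibility criteria allow a mix but do not imply one. Stimulation is given to everyone at about the same hour of the morning (section 10.1), which would fit an effect in one direction. If all deviations are one-sided, the signed acrophase loses nothing and is slightly better (93% versus 89%).
- The objective is to explore, and section 12.1 calls the study descriptive and exploratory.

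A reader might also infer that the criterion should be replaced by distance from a reference. That would trade one blind spot for another, as step 4 shows. The obvious reference, the cancer-free women, is also imperfect: section 8.3.3 requires them to have ISI above 7.

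These objections stand, and they limit both the size of the concern and the remedy. One further objection does not stand: that this is detail for a statistical analysis plan. The protocol itself fixes the variable in section 7.1 and the parameter of interest in section 12.2, and neither measures correction of phase.

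**Conclusion.** The point holds for the acrophase half of the Axis 2 main criterion. The hypothesis is about correction without a stated direction, while the test is about the mean signed shift. When directions are mixed, a null acrophase result does not rule out resynchronisation. In any mix, a signed shift alone does not show it.

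The size depends on the mix. Loss is complete at 50:50, still large at 80:20 (44% versus 89% in the pre-post version), and absent when all women deviate the same way. All power figures rest on assumed SDs, correction fractions, noise, 1:1 allocation and a 5% level. Those for the absolute distance are a favourable case, because they assume one correct phase for all women. The cancellation itself needs none of these values; it follows from the sign of the change. Because the correction is cheap and the hypothesis is the protocol's own, the change should be made.

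**What to change.** Change sections 7.1 and 12.2; no new data are needed.

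1. Keep the signed acrophase and its time × intervention term.
2. Add beside it one prespecified GVS-versus-SHAM test of phase correction in patients. Two forms would serve: (a) a baseline phase × intervention term, with phase taken at T2 or at the start of stimulation; or (b) the change in absolute distance from a reference phase fixed in advance, which takes account of the Horne and Ostberg typology already collected. For (a), the actigraphy from the two weeks before T2 (section 4, Table 1) can supply the baseline.
3. State the expected direction of the acrophase shift, if there is one.
4. Say that any claim of resynchronisation will rest on the phase-correction test and not on the signed shift alone.

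The cost is wording and one more Axis 2 parameter to interpret. Under (b), a reference taken from the 25 cancer-free women carries sampling error, and those women are themselves selected for sleep complaints. The power of either test is unknown until the spread of acrophase is known, because the protocol gives no values for it.
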